### Primary outcome measure: arterial stiffness

Measurements of cfPWV will be performed in accordance with international guidelines.^80^ Previously, cfPWV has been assessed in individuals with SCI.^20 81^ The Vicorder (Smart Medical, UK) system will be used with standard vascular cuffs, which has been shown to be a quick and highly reproducible technique for assessing cfPWV that is operator independent.^82^ Arterial pulse waveforms will be acquired by placing a 100 mm wide BP cuff around the upper thigh of the right leg to measure the femoral pulse and a 30 mm partial cuff around the neck at the level of the right carotid artery. The cuffs will each inflate to 60 mm Hg simultaneously to determine pulse transit time and cfPWV, with waveforms being recorded for at least 3 s while the participant is in the supine position. PWV is calculated as (0.8×*D*)÷Δ*t*, where *D* is the path length distance between the carotid and femoral sites and Δ*t* is the transit time.^80^ Path length is defined as the distance from the suprasternal notch to the top of the thigh cuff as indicated by the manufacturer. The use of cfPWV as a vascular health assessment tool was carefully considered in participants with anterior neck scars or cervical SCI with implanted metal hardware. Individuals with recent surgical scars or contraindications will be excluded from cfPWV assessments to ensure their safety.

### Secondary outcome measures

#### Blood CVD risk biomarkers

Moderate-intensity, upper-body exercise has previously been shown to decrease insulin resistance in individuals with chronic paraplegia.^83^ An 18.5 mL blood sample will be collected from the antecubital vein via a trained phlebotomist following an overnight fast (>10 hours). Serum and plasma samples will be dispensed into 1 mL aliquots and stored at −80°C for batch analysis at a later date using ELISA or an automated analyser (Randox RX Daytona). Biochemical outcomes relating to CVD risk will include triglycerides, total cholesterol, high-density lipoprotein cholesterol, low-density lipoprotein cholesterol, glucose, insulin and C- reactive protein.

#### Left ventricular structure and function

Cardiac structure and function has been shown to rapidly decline between 3 and 6 months during the subacute period of SCI.^54 55^ Furthermore, alterations to cardiac function and mechanics have been reported in individuals with chronic SCI following an exercise intervention.^84 85^ To measure cardiac indices, transthoracic echocardiography will be performed using a Vivid *iq* ultrasound system (General Electric Healthcare, Buckinghamshire, UK) in accordance with recommendations of the American Society for Echocardiography and European Association of Echocardiography.^86^ Images will be stored for offline analysis using specialised computer software (EchoPAC, General Electric Healthcare, Buckinghamshire, UK) by a single analyser. The average of three cardiac cycles will be used to determine left ventricular (LV) structural and functional indices. Indices of LV mechanics will be analysed using two-dimensional speckle-tracking software in accordance with recommended guidelines.^87^

#### Extracranial blood flow velocity and diameter

Functional adaptations to changes in blood flow in the common carotid artery (CCA) have been documented in individuals with SCI.^88^ To further investigate these adaptations earlier postinjury, blood velocity and vessel diameter of the right CCA, internal carotid artery (ICA), external carotid artery (ECA) and vertebral artery (VA) will be measured using a 12 MHz linear array probe (Terason uSmart 3300, Teratech, Burlington, Massachusetts, USA). The participant’s head will be turned slightly to the left side. Pulse-wave Doppler will measure peak blood velocity and B-mode will measure arterial diameter. The insonation angle will be set at 60° and will be unchanged throughout the collection of data.^89^ The ICA and ECA blood velocity and vessel diameter will be measured at least a distance of 1 cm from the carotid bulb to avoid turbulent flow patterns. VA blood velocity will be measured between the C4 and C6 vertebral level. Vessel location is based on an individual’s unique anatomical characteristics and will allow for reliable acquisition and repeatability on each assessment. Images will be stored for offline analysis using specialised software (Cardiovascular Suite 4, Quipu, Italy). Mean blood velocity will be measured from the velocity time integral.^90^ Mean shear rate will be calculated by four times peak velocity divided by vessel diameter.^91^ Subsequently, blood flow will be calculated using half the peak envelope velocity (ie, mean blood velocity) multiplied by the cross sectional area of the vessel.^92^

#### Resting heart rate variability

Resting HR will be measured continuously via five-lead ECG (Model 26T, ADInstruments, Colorado Springs, Colorado, USA). HRV will be measured in the time (eg, HR, SD of R-R intervals and the root mean square of successive R-R interval differences), frequency (eg, very-low-frequency, low-frequency, high-frequency and total power) and non-linear (eg, Poincaré plot analyses) domains. HRV represents a measure of the variation in time between heart beats as a time interval between the R waves of the QRS complexes,^93^ which are associated with overall health status due to increasing sympathetic tone.^94^ Before data are collected, each participant will rest in a supine position for at least 5 min in a quiet room. Resting HR will be recorded with unpaced, spontaneous breathing. Subsequently, in response to auditory cues for inspiration and expiration (ie, resonant breathing^95^), participants will record at least 5 min of data while they pace their breathing at a frequency of 15 breaths per min (0.25 Hz).^96^ Different breathing patterns have been shown to influence HRV metrics and therefore cardio–vagal balance.^97^

#### Health-related quality of life

Shoulder pain will be assessed at A1–A4 and weekly between A2 and A3 using the Wheelchair User’s Shoulder Pain Index (WUSPI)^39^ for individuals in the ACET group. The performance-corrected WUSPI score (PC-WUSPI) will be used as it accommodates participants who are unable to undertake certain functions. This correction multiplies the average response for all items by the number of questions attempted, with higher values indicating a greater degree of perceived shoulder pain. Bodily pain severity and interference will be assessed using the two-item Short Form-36 (SF-36) Pain subscale, capturing the past 4 weeks. Item scores will be combined into a single composite score (0–100 scale); lower scores indicate greater pain. Pain derived from the SF-36 subscale is commonly used in SCI clinical settings.^98^ Furthermore, experts working in the field have recommended this measure as a minimum to quantify pain in clinical trials,^99^ and it has shown acceptable reliability and validity in the SCI population.^100^ Fatigue^101^ will be measured via the Fatigue Severity Scale.

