**Figure 3 F3:**
[figure not shown]
Study flow chart. Following participant identification and initial assessments (**A1**) at MCSI, assessments will be repeated after a period of standard care (which will primarily involve bed rest depending on the severity of injury) (**A2**). Participants thereby act as their own controls. At this point, participants will be randomised to receive either standard of care inpatient rehabilitation (CONTROL) or standard of care inpatient rehabilitation plus 30 min of ACET, 3–5 times per week (ACET INTERVENTION) for 10 weeks, with postassessments (**A3**). 6 months after discharge (~36 weeks) into the community, follow-up HRQOL assessments will be carried out (**A4**). ABPM, ambulatory blood pressure monitoring; ACET, arm-crank exercise training; HRQOL; health-related quality of life; SCI, spinal cord injury.

The A1 assessment serves as a time point for characterising key outcome measures on admission into inpatient rehabilitation, providing a baseline of cardiovascular health. Given the significant adjustments participants face following this life-changing injury, we have streamlined some of the secondary outcome measure assessments between A1 and A2 to minimise participant burden. Therefore, rehabilitation physical activity energy expenditure, 24-hour BP monitoring and motor function assessments will be conducted only once between A1 and A2, as outlined in table 2. The rationale for having both A1 and A2 assessments for the cardiovascular measures and HRQOL questionnaires is twofold: (1) to gauge any variability or changes in responses between the time close to admission (A1) and the adjustment to their new injury (A2; for example, following initial standard of care therapy sessions) and (2) to establish multiple baselines for these outcome measures, thereby allowing participants to serve as their own controls and capturing the inherent variability in these outcomes.

**Table 2 T2:** Schedule of enrolment, interventions and assessments

Study procedures	Screen	Baseline(A1)	A1–A2	Preintervention/randomisation(A2)	Training sessions	Final week	Postintervention(A3)	Community follow-up(A4)*
Visit (V)	V1	V2	V2/V3	V3/V4	V4/V5–V45/V46	V46/V47	V47/V48	V48/V49
Eligibility								
Informed consent	X							
Medical history/demographics	X							
Changes in medication/health status				X			X	
Pregnancy screening	X							
International Standards for Neurological Classification	X						X	

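### The PC-WUSPI scoring rule, as printed, does not correct for activities a participant cannot perform, so the score can move with the number of items attempted when pain per activity is unchanged

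*Protocol article*

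**What the plan says.** The Health-related quality of life section of the protocol article gives the reason for the score: "The performance-corrected WUSPI score (PC-WUSPI) will be used as it accommodates participants who are unable to undertake certain functions". The next sentence gives the rule: "This correction multiplies the average response for all items by the number of questions attempted". It also fixes the direction of the score, "with higher values indicating a greater degree of perceived shoulder pain".

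The same section and Table 2 schedule the WUSPI at A1, A2, A3 and A4, and weekly during the training period. The Table 2 footnote limits A4 to the HRQOL questionnaires and the WUSPI. The article gives no other scoring rule for the instrument and does not state how many items it has.

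**The concern.** A correction for activities that cannot be performed has to separate two things: how much the attempted activities hurt, and how many were attempted. The printed rule multiplies by the number attempted and so puts back the quantity it is meant to remove.

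The number attempted could plausibly change in this trial. Eligibility runs from C5 to T12. The Figure 3 legend describes care between A1 and A2 as largely bed rest, depending on severity. A3 follows ten weeks of rehabilitation, and A4 takes place after discharge. A participant who regains activities could therefore appear to have more shoulder pain, and one who gives up activities could appear to have less.

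The WUSPI is the only shoulder-specific pain measure in the plan. The Background names overuse of the arms and shoulders as a source of pain after SCI, and the intervention is arm cranking. A score that mixes pain with activity count would be hard to interpret on that question.

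**Working it through.** **Inputs.** The rule, its purpose and its direction come from the Health-related quality of life section. The article gives no worked example, so there is no stated figure to reproduce. The item count, the numbers attempted and the pain levels below are assumptions for illustration.

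**Notation.** K = items on the scale; k = items attempted; S = sum of responses on attempted items; m = S/k = mean pain per attempted item.

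**Algebra.**
- Reading 1, average over attempted items: (S/k) × k = S, the uncorrected total.
- Reading 2, average over all K items with unattempted items contributing zero: (S/K) × k = S × k/K, at or below the raw total.
- Rescaled score: (S/k) × K = m × K, which does not contain k once m is fixed.

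At constant m, Reading 1 is proportional to k and Reading 2 to k². The percentage change depends only on the ratio of attempted counts, not on K or m.

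**Illustration (K = 15, m = 3, both assumed).**

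| Rule | k = 8 | k = 14 | Change |
|---|---|---|---|
| Raw sum S | 3 × 8 = 24 | 3 × 14 = 42 | +75% |
| Reading 1 | (24/8) × 8 = 24 | (42/14) × 14 = 42 | +75% |
| Reading 2 | (24/15) × 8 = 12.8 | (42/15) × 14 = 39.2 | +206% |
| Rescaled | (24/8) × 15 = 45 | (42/14) × 15 = 45 | none |

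**Range over the assumptions (m = 4).**
- From 60% of items attempted to all of them, Reading 1 goes from 24 to 40 (K = 10), 36 to 60 (K = 15) or 48 to 80 (K = 20), each +67%. Reading 2 goes from 14.4 to 40, 21.6 to 60 or 28.8 to 80, each +178%. The rescaled score stays at 40, 60 and 80.
- For a smaller change, 12 to 15 items with K = 15, Reading 1 goes from 48 to 60 (+25%) and Reading 2 from 38.4 to 60 (+56%).
- If k does not change, neither reading distorts the trend.

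**Opposite direction.** If m rises from 3 to 4 while k falls from 14 to 8, Reading 1 falls from 42 to 4 × 8 = 32, although pain per activity rose by a third. With K = 15 the rescaled score rises from 45 to 60.

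**Pain-free new items.** If k goes from 8 to 14 and the six added items score zero, S stays at 24. Reading 1 stays at 24. Reading 2 still rises, from 12.8 to 24 × 14/15 = 22.4.

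**The case against.** The strongest reply is that this is a slip of wording. The article names a recognised score and states its purpose correctly; one phrase, the number attempted in place of the number of items on the scale, is out of line. The article cannot show whether the trial's scoring follows the printed formula. That stands: what can be said is that the sentence is wrong as printed. A reader might infer that the trial's scores will be wrong, but the document does not establish it.

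The consequences are also conditional. A reader might infer that recovering participants will show worsening pain. That needs the number of attempted items to change and, under the first reading, the added items to carry some pain. The article gives no data on either.

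A reader might further infer a bias between the arms. That needs WUSPI data from both arms and a different change in activities attempted. The sentence scheduling the WUSPI ends by referring to individuals in the ACET group, and it is unclear whether this limits only the weekly measurements or all of them. A1 and A2 precede randomisation, Table 2 restricts no visit by arm, and the Assessments section plans a comparison of HRQOL outcomes between the groups at A4, so control data are likely but not certain. Similar changes in both arms would affect time trends far more than the comparison.

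Finally, the primary outcome, sample size and power rest on cfPWV and are untouched. SF-36 bodily pain is also unaffected, though it is not shoulder-specific. No withdrawal or safety rule in the article uses a PC-WUSPI value. These points limit the severity; none makes the printed rule correct.

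**Conclusion.** The rule is wrong as written and should be fixed. Under either reading of the average, it does not correct for activities a participant cannot perform, which is the only reason given for using it. That conclusion is algebraic and needs no assumption about the instrument.

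The size of any distortion is not known. At constant pain per activity it equals the proportional change in items attempted under Reading 1, and more under Reading 2: in the examples, 25% to 75% and 56% to 206% respectively. The 75% figure is an illustration with assumed counts and should not be read as an expected bias. Time trends could be distorted; the comparison between arms could be too, but only if both arms complete the WUSPI and differ in activities regained. Because this is a secondary score that can be recomputed from item responses, the error is reversible at analysis.

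**What to change.** Replace the scoring sentence with: PC-WUSPI = (sum of responses / number of items attempted) × total number of items on the scale, and state that total. The mean over attempted items serves equally well, since it differs only by a constant factor.

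Apply the rule at every time point, including the weekly assessments, and recompute any scores already derived with the printed rule. Report the number of items attempted by visit, and by arm where both arms are measured, so that readers can see whether pain per activity or the range of activities has changed. State in the same edit whether the control group completes the WUSPI at A3 and A4.

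The cost is one or two sentences and a one-line change to the scoring, using the item responses the questionnaire already yields. No new data are needed.

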#### Cognitive function

A shortened neuropsychological test battery will be used that includes the Digit Span and Symbol Digit Modality Test (SDMT) to give a global indication of cognitive function. These tests will be delivered orally to account for motor function difficulties in individuals with higher-level SCI. Participants will verbally respond to the test stimuli with the same, trained assessor noting down their answers accordingly. The forward digit span measures attention and short-term memory, whereas the backward digit span task measures visuospatial integration and working memory. The SDMT measures complex visual tracking and working memory. Both of these cognitive tests have previously demonstrated good-to-excellent reliability when used in the SCI population.^102^ Previous work on cognitive health following SCI showed that up to 64% of injured individuals were cognitively impaired,^36^ with a 13-fold increased risk of cognitive impairment compared with non-injured individuals.^41^ Experimental SCI has been associated with structural alterations and endothelial dysfunction in cerebral arteries that possibly contribute to reduced cerebral blood flow and vascular cognitive impairment.^103^ While decentralised cardiovascular autonomic control has been implicated in cognitive and cerebrovascular deficits post-SCI,^104^,^106^ subclinical arterial stiffness has also been speculated to accelerate age-related cognitive decline.^46^

#### BP monitoring over a 24-hour period

Periodic (daytime: every 15 min; night-time: every hour) brachial BP measurements will be recorded using an ambulatory BP monitor (IEM Mobil-O-Graph). 24-hour ambulatory BP monitoring (ABPM) will be used to capture BP variability,^107^ plus will allow for the determination of nocturnal dip (considered a prognostic indicator for CVD^108^). As a diminished autonomic control over the cardiovascular system can cause profound BP instability, particularly in individuals with higher neurological levels of SCI, the use of ABPM allows for insight into circadian BP profiles and can provide prognostic values for cardiovascular morbidity and mortality in the SCI population.^109^ Furthermore, increased BP variability is a significant and independent predictor of mortality and cardiovascular events in the general population,^110^ and an increased frequency of hypotensive events over 24 hours has been associated with arterial stiffening^20^ and impaired cerebrovascular reactivity^106^ in individuals with SCI.

#### Rehabilitation energy expenditure and free-living heart rate variability

Participants will wear an individually calibrated multisensor device (Actiheart, Cambridge Neurotechnology, Papworth Everard, UK) for at least 4 days, which has been shown to be a sufficient duration to measure energy expenditure components in individuals with SCI.^31^ The Actiheart, which is worn on the chest and incorporates tri-axial accelerometry and HR, has been demonstrated to accurately and precisely estimate physical activity energy expenditure in wheelchair users.^111^ This device provides information on the number of minutes spent performing sedentary, light, moderate and vigorous-intensity activities.^112^ The Actiheart also has the capability of measuring HRV in different domains (as described above), with the advantage of the measures being taken over a 4-day period to provide insight on the integrity and responsiveness of the autonomic pathways in response to external stimuli.^17^

#### Cardiorespiratory fitness

Peak oxygen uptake (V̇O_2peak_) and peak power output (PO_peak_) will be determined using a graded CPET performed on an arm-crank ergometer until volitional exhaustion. Alternatively, to address the challenges of peak aerobic fitness testing in participants clinically determined to not be able to complete a maximal test in the opinion of the CI (a certified exercise physiologist), the Six-Minute Arm Test (6MAT) may be used. The 6MAT, which has been shown to reliably assess aerobic capacity in individuals with SCI, will be used to predict V̇O_2peak_ using an established regression equation.^113^ This approach will accommodate those unable to perform maximal exertion tests. Expired gases will be collected using a calibrated, portable metabolic cart (COSMED K5, Italy). BP will be measured before and after exercise. HR will also be measured throughout (rest, exercise and following 5 min of recovery). HR recovery (HRR) data will be used to determine vagal reactivation (fast phase) and sympathetic withdrawal (slow phase). Reduced HRR has been linked with increased cardiovascular morbidity and all-cause mortality.^114^ At least 3 days prior to performing the A2 CPET, participants in both groups will perform a familiarisation arm-crank exercise session at a self-prescribed intensity for 20 min. Therefore, participants will either perform a maximal exertion test or 6MAT for assessment of their cardiorespiratory fitness at the A1-A2 and A3 time points, which will not impact their randomisation to either arm of the trial.

#### Motor function

Prior work has indicated improved trunk control after upper-body exercise interventions, such as ACET.^68 115 116^ While the exact underlying mechanisms remain unknown, a possible explanation is to use the shared control mechanism between arm and trunk muscles which facilitate corticospinal excitability projecting to the trunk muscles during contractions of the arm muscles.^68 117^ To determine the effect of ACET on trunk motor function in subacute SCI, static and dynamic sitting balance for trunk stability will be evaluated using the Function in Sitting Test (FIST)-SCI.^118^ Individuals with SCI have ranked trunk stability as the third highest priority to improve life quality^119^ and this has been linked to the ability to perform functional activities after SCI.^118 120 121^ Muscle strength will be quantified by a hand-held dynamometer (Jamar Plus+, Performance Health, Warrenville, Illinois, USA) and reported in kilograms for participants with paraplegia only. These outcomes will capture loss or recovery in motor function and any improvements in strength, which is related to functional ability to perform activities of daily living.^122^

#### Feasibility outcomes

To obtain information about the usability and satisfaction with ACET in the subacute inpatient rehabilitation setting, participants will complete the Participant Evaluation of Feasibility and Acceptability Questionnaire,^123^ which consists of six items arranged on a Likert scale ranging from 1 to 5 and has been used previously for exercise interventions in individuals with SCI.^124^ Four open-ended questions have been developed and added to the instrument to identify facilitators for exercise; challenges/barriers to exercise; benefits experienced from participating in the ACET intervention; and suggestions for strategies to support individuals with subacute SCI to engage in ACET.

Framework analysis will be used to analyse the responses to the four open-ended questions using the NVivo qualitative research software (NVivo 12) to organise the data. A predetermined framework consisting of the four question topics (facilitators, barriers, benefits and recommendations) will be employed as an initial coding frame.^125 126^ This questionnaire will only be completed at A3 (see figure 1).

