### Exercise interventions to improve cardiovascular health in individuals with subacute SCI

The cardiovascular stress during inpatient rehabilitation in the UK remains to be objectively quantified, as we have done previously to capture habitual free-living behaviours in community-dwelling individuals with SCI.^31^ Preclinical evidence indicates that early administration of exercise following experimental SCI leads to more pronounced cardiohaemodynamic benefits than delayed exercise administration.^53^ This is likely important in the clinical setting as literature indicates that individuals with SCI exhibit significant reductions in cardiac function within the first 6 months following injury.^54 55^ Arm-crank exercise training (ACET) is an inexpensive and widely used exercise modality for individuals with SCI^56^ that has been shown to improve cardiorespiratory fitness.^57^ Despite the amount of evidence supporting the benefits of ACET for cardiovascular health in chronic (>12 months) SCI,^57^,^59^ there is little understanding of whether the same effect can be expected in subacute SCI and whether an exercise intervention initiated in this stage postinjury mitigates declines in cardiac structure and function.^60^ A recent systematic review indicated very low levels of evidence for the benefits of exercise in the subacute phase following SCI,^58^ primarily due to the limited and poorly designed research studies available.

Given the known benefits of ACET for individuals with chronic SCI, this study aims to investigate the effects of exercise on cardiovascular health parameters in patients with subacute SCI. It is also essential to qualitatively assess the feasibility and implementation of ACET in the subacute rehabilitation setting. Understanding both patient and healthcare provider/staff perspectives on receiving and delivering an ACET intervention, respectively, is crucial for the development of effective rehabilitation tailored to individuals with SCI. While regular physical activity has been reported to have significant health benefits for individuals with SCI,^61^ it is equally as important to consider the potential overburdening of inpatients alongside their standard of care, as well as both the clinical and cost-effectiveness of promoting additional prescribed aerobic upper-body exercise in the rehabilitation pathway.^62^

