### Trial objectives

We aim to determine whether the addition of ACET to standard of care treatment during inpatient rehabilitation within the subacute period following SCI has beneficial effects over the current standard of care (control group, CON) rehabilitation on arterial stiffness (measured via cfPWV) and secondary health outcomes: (1) blood biomarkers related to CVD, (2) cardiac structure and function, (3) extracranial vasculature, (4) HRQOL, (5) cognitive function, (6) physical activity level, (7) cardiorespiratory fitness, (8) motor function and (9) feasibility outcomes in individuals with subacute SCI. In comparison to CON, we hypothesise that the physical and metabolic stimuli of ACET will maintain cfPWV at a level that is comparable to normative age-matched values reported in the general population.^63^

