Adherence will be periodically assessed every 3 weeks to determine the feasibility of the participant achieving the minimal amount of exercise sessions during the 10-week period. This pragmatic approach accounts for the associated complexities of working with this population in the subacute setting that may result in exercise sessions being missed. Participants will be given the option to catch up with missed exercise sessions during subsequent weeks. If a participant misses a period of 3 weeks’ worth of consecutive exercise sessions (n=9) and is unable to compensate after review with a member of the study team, then they will be withdrawn from the trial due to non-compliance (figure 2).

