#### Longitudinal qualitative data collection

Participants in the ACET group will be invited to attend a one-to-one semistructured interview at completion of the intervention (A3) to discuss their views on the intervention received and the impact of the intervention on their recovery. The discussion will cover the study protocol, effects of the intervention on their health in the short term and the feasibility of administering the intervention in a hospital setting. The findings of the analysis of the four open questions will be used to probe further during the interviews.

In-person focus groups will also be performed with staff (clinicians, occupational therapists and physical therapists) involved in clinical care/rehabilitation of patients at RJAH on study completion to ascertain the acceptability of the intervention, trial design and outcome measures, as well as the staff’s experiences during the trial. Prior to taking part in the focus group, RJAH staff will complete a screening survey, requesting descriptive characteristics such as age, sex, qualifications, job role and level of experience. A trained moderator will run the interviews/focus groups and data will be audio recorded via a secure password protected digital recording device. These interviews/focus groups will address the aforementioned themes via a semistructured interview schedule.^127^ The recorded discussions will subsequently be transcribed verbatim and analysed employing the same framework analysis protocol used in the analysis of the open-ended questions as an initial coding frame.^126^

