### Power calculation and sample size

We aim to recruit 42 participants for this study. This sample size was based on the effect size drawn from the CHOICES multicentre RCT.^129^ Our a priori power calculation indicated that a sample size of 32 individuals with SCI, 16 in each group, is sufficient to detect a between-group interaction effect for cfPWV, using a two-way repeated measures ANOVA with 95% power and a 5% level of significance to detect exercise group differences of ≥1 m/s. Our target effect size of 1 m/s aligns with reported exercise intervention effects in high-risk populations and represents a clinically meaningful improvement, as each 1 m/s increase in cfPWV corresponds to a 15% increased risk of cardiovascular mortality.^130 131^ A recent study found that ~16% of participants who were randomly assigned to a 5-week ACET intervention in the subacute setting discontinued the intervention.^132^ To account for the longer intervention duration in this trial, a more conservative (30%) dropout rate was estimated. Hence, 42 participants in total will be enrolled in the study.

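### Participants' own views on the feasibility of arm-crank training are sought only at A3, so those withdrawn or lost before then are not asked.

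*Protocol article*

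**What the plan says.** The Trial objectives section lists feasibility as the last of nine secondary outcomes. The background section on exercise interventions gives it more weight: "It is also essential to qualitatively assess the feasibility and implementation of ACET in the subacute rehabilitation setting".

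Two instruments collect the participant's own view.

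- **Questionnaire** (Feasibility outcomes): six items scored 1 to 5, plus four open questions on facilitators, barriers, benefits and suggestions. On timing: "This questionnaire will only be completed at A3 (see figure 1").
- **Interview** (Longitudinal qualitative data collection): "Participants in the ACET group will be invited to attend a one-to-one semistructured interview at completion of the intervention (A3").

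Table 2 marks both in the A3 column and nowhere else.

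The Arm cycle ergometry training section sets a withdrawal rule. If a participant misses nine consecutive sessions, three weeks' worth, and cannot compensate after review, "then they will be withdrawn from the trial due to non-compliance". On expected loss, the Power calculation and sample size section reports that in a study of a shorter programme about "16% of participants who were randomly assigned to a 5-week ACET intervention in the subacute setting discontinued the intervention", and for this trial "a more conservative (30%) dropout rate was estimated".

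**The concern.** The withdrawal rule acts on whether a person could or would do the exercise, and that is what a feasibility outcome is meant to describe. If views are gathered only at A3, the group that answers has been selected partly on the outcome itself. The barriers met by people who could not continue are the ones most useful for designing later programmes, and the schedule has no point at which those people are asked. The Discussion counts the post-intervention interviews as a strength of the trial, so the gap bears on a claim that the authors intend to make. An analysis plan could not repair it, because views that were not collected cannot be recovered.

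This is separate from the effect of withdrawals on the between-group comparison of pulse wave velocity.

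**Working it through.** **Inputs from the protocol article (Power calculation and sample size):** 32 participants required, 16 per group; 42 enrolled; 30% planned dropout; about 16% discontinuation in the cited 5-week study. Equal allocation gives 42 / 2 = 21 in the ACET group.

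**The plan's own figure.** 32 x 1.30 = 41.6, which rounds up to 42, so 42 is obtained by adding 30% to 32. Dividing by the expected retention would give 32 / 0.70 = 45.7, that is 46. That is a separate matter. Here 42 is taken as the planned enrolment.

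**ACET participants not reaching A3,** 21 x d:

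- d = 0.30: 21 x 0.30 = 6.3, about 6 lost and about 15 answering
- d = 0.16: 21 x 0.16 = 3.4, about 3 lost and about 18 answering

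**Do other sources supply the missing views?**

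| Source | Section | Asks withdrawn participants for their views? |
|---|---|---|
| Adherence review every 3 weeks | Arm cycle ergometry training | No, it tracks sessions achieved |
| Reasons for declining the extra sessions offered at 4 and 7 weeks | Arm cycle ergometry training | No, it covers the optional sessions only |
| Staff focus groups | Longitudinal qualitative data collection | No, staff views |
| A4 remote follow-up | Table 2 footnote | No, quality-of-life and shoulder-pain questionnaires only |

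**Possible bias.** Let p_c be the proportion of completers who find ACET acceptable and p_d the proportion among those lost. The figure for everyone allocated to ACET is (1 - d) x p_c + d x p_d. The completer figure differs from it by d x (p_c - p_d).

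- Ceiling (p_c = 1, p_d = 0): 30 percentage points at d = 0.30, 16 at d = 0.16.
- Floor when those lost are no more favourable than completers (p_d = p_c): 0.
- Illustration only, with p_c = 0.90 and p_d between 0 and 0.50, both assumed. At d = 0.30 the difference is 0.30 x 0.90 = 27 points down to 0.30 x 0.40 = 12 points. At d = 0.16 it is 0.16 x 0.90 = 14 points down to 0.16 x 0.40 = 6 points.

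The document gives neither p_c nor p_d, so the actual size cannot be computed.

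**The case against.** Several points on the other side stand.

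- **Feasibility is not measured at A3 alone.** A reader might infer that all feasibility data come from completers. The document does not support this: adherence reviews, reasons for declining optional sessions, training logs kept by those exercising at home, weekly shoulder-pain scores and staff focus groups all contribute, and several accrue on people who later stop. Only participant-reported acceptability and barriers are confined to A3.
- **Stopping exercise is not the same as leaving the trial.** A reader might infer that anyone who discontinues is never asked. A3 is also defined as a 10-week time point, and nothing bars a person who has stopped cranking but remains in the trial from completing the questionnaire. The withdrawal rule is narrow, with catch-up sessions and home ergometers to avoid it. The gap is firm only for those withdrawn or lost before A3.
- **Overstatement is not established.** It requires that those lost view ACET less favourably. The document names pressure sores, urinary tract infections and other complications as things that interrupt rehabilitation, and losses unrelated to ACET would cause little or no bias.
- **The 30% is a deliberately cautious allowance for the whole trial,** not a forecast for the ACET group.

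It can also be said that a condensed article may leave exit procedures to the full protocol, and that the word on timing only contrasts this questionnaire with those repeated at several visits. This carries less weight. The article restricts the timing affirmatively, table 2 agrees, and the interview is separately placed at the end of the intervention.

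**Conclusion.** The point holds in a limited form. The article fixes both participant-reported instruments at A3 and withdraws some non-compliant participants before then, so people withdrawn or lost are not asked what made ACET unworkable or unacceptable to them. That is about 6 of 21 at the planned dropout and about 3 of 21 at the cited rate, assuming equal group sizes and that the rate applies to the ACET group.

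The likely direction favours ACET, because one route out of the trial is failure to do the exercise. The size is unknown. Even with no bias in the scores, the account of barriers would lack the people who could not continue. No hypothesis test or stated threshold depends on these data, so this is a worthwhile improvement to a secondary objective and not a threat to the primary result.

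**What to change.** In the Feasibility outcomes and Longitudinal qualitative data collection sections, and in table 2, state that the existing questionnaire with its four open questions and the interview invitation are offered to every ACET participant at A3 or at discontinuation or withdrawal, whichever comes first, remotely if needed. Report the results for completers, for non-completers and for all ACET participants together, with the number not reached.

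The change needs no new instrument and leaves the training schedule and the withdrawal rule untouched. The article already plans remote contact for A4. The cost is a protocol wording change and some 3 to 6 extra short contacts. Participation stays voluntary, so response among those who withdraw will be incomplete.
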